##### Intrinsic foot muscle strength

To measure the strength of supporting the foot arch, the intrinsic foot muscle strength will be collected during a special functional movement known as ‘doming’. The measurement of intrinsic foot muscle strength will be conducted on custom-built apparatuses with a dynamometer, which has been reported in previous studies (ICC = 0.949, SEM = 0.883 kg) [36, 37]. The participants will be instructed to perform the doming movement by activating muscles to pull the metatarsal heads towards the heel (also known as the short-foot exercise). Before the test, the assessor will check the foot placement to ensure that the dynamometer is rested against the dorsum of the foot, just above the navicular tuberosity. Participants will be asked to perform the doming to a 3-s maximal voluntary contraction against the dynamometer. Only the data of correct movement will be recorded. The mean values of the three trials will be used for analysis. The value of foot muscle strength will be measured at the points of baseline (week 0), post-intervention (week 12) and follow-up (week 24). The scores of berg scale will be shown as mean and standard deviation.

##### Foot arch function

The navicular drop test, which have been used in older adults [38], is one clinical examination commonly used to evaluate foot arch function [39, 40]. It will be conducted to determine the effect of intrinsic-foot-muscle exercise on supporting the foot arch. First, with the participants standing barefoot on the floor, an experienced investigator will mark the navicular tuberosity. With the palpation of the lateral and medial aspect of the talar dome, the investigator will invert and evert the foot carefully until the talus is in a central position. The distance between the navicular tuberosity and the floor will be measured with a vernier calliper. Then, the investigator will repeat the test process while the participants stand in a non-weightbearing position. The difference in the navicular tuberosity heights will be calculated for analysis. The outcome of the navicular drop test will be measured at the points of baseline (week 0), post-intervention (week 12) and follow-up (week 24). The scores of berg scale will be shown as mean and standard deviation.

### Criteria for discontinuing or modifying allocated interventions {11b}

Withdrawal from the study will be allowed on the following:
The subject makes such a request.The subject develops a serious disease, such as heart disease or stroke. He or she is unsuitable to continue the participation after the determination of the main investigator.The subject reports serious adverse events in this study. Serious adverse events refer to the unexpected events that may require medical or surgical intervention, such as musculoskeletal problems.

### Relevant concomitant care permitted or prohibited during the trial {11d}

During the trial, the participants will be informed not to take part in any other regular balanced promotion programmes and maintain their previous lifestyle.

### Provisions for post-trial care {30}

Not applicable. There is no anticipated harm and compensation for trial participation.

### Participant timeline {13}

Figure 3 shows the time schedule of enrolment, visits for participants, intervention and assessments.

**Fig. 3 Fig3:**
[figure not shown]
Schedule of study procedures. *IFM group, intrinsic-foot-muscle exercise combined the lower extremity resistance training group; EFM group, extrinsic-foot-muscle exercise combined the lower extremity resistance training group; Control group, lower extremity resistance training group

#### Sample size {14}

To the best of our knowledge, no study has been designed to investigate the effect of intrinsic-foot-muscle training on postural stability in older adults. Therefore, the G*POWER software 3.1 software was used to calculate the suitable sample size for the multivariate of analysis for repeated measurements (MANOVA) test using 3 independent groups with settings of *α* = 0.05, power (1 − β) = 0.80 and standardised medium effect size = 0.25 (the partial eta squared). The power analysis showed that three independent groups with 98 participants in total were the required sample size. Considering the drop-out rate, 40 participants in each group will be recruited for this study.

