**Fig. 1 Fig1:**
[figure not shown]
Flow diagram of study design. IFM group, intrinsic-foot-muscle exercise combined the lower extremity resistance training group; EFM group, extrinsic-foot-muscle exercise combined the lower extremity resistance training group; Control group, lower extremity resistance training group

Eligible participants will be randomised at a 1:1:1 ratio to enrol in one of the three groups. Three intervention programmes will be included in this study, namely, intrinsic-foot-muscle exercise combined with lower extremity resistance training (IFM), extrinsic-foot-muscle exercise combined lower extremity resistance training (EFM) and lower extremity resistance training programme (Fig. 1).

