### Statistical methods

#### Statistical methods for primary and secondary outcomes {20a}

The full analysis set includes all randomised participants who take at least one session of intervention. If follow-up data of primary outcomes are missing, last observation carried forward method and multiple imputation method will be carried out to adjust for the missing data and intention-to-treat analysis was utilised.

The statistical analyses, including calculation of the mean and standard deviation, will be performed using SPSS statistical software (version 20.0 for Windows; SPSS, Inc., Chicago, USA). Descriptive statistics will be used separately for every group and for the total sample. Continuous variables will be presented as means, standard deviation, and 95% confidence intervals. And categorical variables will be expressed percentages and absolute numbers. The normality of distribution for quantitative data will be assessed using the Kolmogorov–Smirnov test. Chi-squared tests or Fisher’s exact tests (categorical variables) and one-way ANOVA or nonparametric tests (continuous variables) will be used respectively to test the demographic differences among the IFM, EFM and control groups.

The average effects (difference between the three groups) for all the variables will be estimated using general linear models of multivariate of analysis for repeated measurements (MANOVA) test, which incorporates the three intervention groups (control * IFM * EFM), time (baseline * post-intervention * follow-up) and group-time interaction. To examine the effect size of the treatment, the partial eta squared will be calculated. Bonferroni’s post hoc test will be applied to identify the differences. Once the significant difference of group-time interaction is detected, the one-way repeated measurements will be performed to determine the difference of effect within each group (pre-intervention, post-intervention and follow-up). Statistical significance will be set at 0.05 for all analyses. Analysis will be carried out by an independent researcher.

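### The planning effect of 0.25 is labelled partial eta squared, but the stated N of 98 follows only if 0.25 is an f-type effect size (partial eta squared about 0.06)

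*Protocol article*

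**What the plan says.** The section Sample size {14} reports a G*Power 3.1 calculation for a "multivariate of analysis for repeated measurements (MANOVA) test using 3 independent groups", with "settings of *α* = 0.05, power (1 − β) = 0.80" and a "standardised medium effect size = 0.25 (the partial eta squared"). The result is that "three independent groups with 98 participants in total were the required sample size". Recruitment is then set at 40 per group, 120 in all, to allow for drop-out; no drop-out rate is given.

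That section states neither the number of repeated measurements nor which effect is tested. Both can be taken from Statistical methods {20a}, where the model contains the three groups, "time (baseline * post-intervention * follow-up) and group-time interaction". The same section adds: "To examine the effect size of the treatment, the partial eta squared will be calculated".

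Nowhere does the article describe 0.25 as f or f(V).

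**The concern.** Partial eta squared and f are different scales for the same effect, linked by f² = η²/(1 − η²). A value of 0.25 on one is far from 0.25 on the other. The section calls the effect medium and also calls it a partial eta squared of 0.25, and the stated N can be checked to see which scale was used.

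Two things are at stake. First, the section says that no earlier study of this training in older adults was available, so the assumed effect is the whole justification for the trial size. Anyone repeating the calculation from the inputs as printed gets a far smaller number and could conclude that 120 participants are not justified. Second, the trial will report its results as partial eta squared. An observed value near 0.06, which is what 98 participants were sized to detect, could be read as a four-fold shortfall against a planned 0.25.

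**Working it through.** **Inputs**
- From Sample size {14}: alpha 0.05, power 0.80, 3 groups, effect size 0.25, N = 98.
- From Trial design {8}: 1:1:1 allocation.
- From Statistical methods {20a}: 3 time points and the group-by-time interaction. Using these two in the sample size calculation is an inference.

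**Formula.** For the repeated-measures MANOVA within-between interaction (Pillai trace) with k = 3 groups and m = 3 measurements:
- s = min(k − 1, m − 1) = 2
- df1 = (k − 1)(m − 1) = 4
- df2 = s(N − k − (m − 1) + s) = 2(N − 3)
- non-centrality λ = N · s · f(V)²
- power = probability that a non-central F(df1, df2, λ) exceeds the 5% critical value of the central F.

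**Step 1: reproduce the stated N with 0.25 as f(V)**
- N = 97: df2 = 188, λ = 97 × 2 × 0.0625 = 12.125, power 0.7957.
- N = 98: df2 = 190, λ = 98 × 2 × 0.0625 = 12.25, power 0.8005.

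The smallest N reaching 80% is 98, an exact match.

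**Step 2: take the label literally, partial eta squared = 0.25**
- f = √(0.25/0.75) = 0.577, so f² = 0.333.
- N = 20: df2 = 34, λ = 20 × 2 × 0.333 = 13.33, power 0.787.
- N = 21: df2 = 36, λ = 21 × 2 × 0.333 = 14.0, power 0.813.

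The required N is 21. At N = 98 the power would exceed 0.9999.

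**Step 3: other readings of 0.25 in the same test**

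| Reading of 0.25 | Required N |
|---|---|
| f(V) | 98 |
| f squared | 27 |
| Pillai V | 45 |
| partial eta squared | 21 |

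**Step 4: does the answer depend on the choice of test?**
- With 0.25 as an f-type value, basing λ on df2 gives 101. A univariate between-groups test gives 106 (3 visits, correlation 0.5) or 100 (4 visits, correlation 0.5). A global MANOVA on 2 responses gives 98 as well.
- With 0.25 as partial eta squared, the interaction test with λ based on df2 gives 24. Across all the variants tried (2 to 4 measurements, multivariate and univariate repeated-measures tests with correlations from 0 to 0.7, one-way ANOVA), none needed more than 35.

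The match to 98 therefore does not identify the test uniquely, but every variant that lands at or near 98 uses 0.25 as an f-type value.

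**Step 5: size of the discrepancy**
- f = 0.25 gives partial eta squared 0.0625/1.0625 = 0.059.
- Variance-explained scale: 0.25/0.0588 = 4.25.
- f scale: 0.577/0.25 = 2.3.

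**Step 6: recruitment.** 1 − 98/120 = 18.3%, the drop-out that 120 recruited would absorb.

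**The case against.** The strongest reply is that this is a slip in a parenthesis with no effect on the trial. N, the allocation, alpha, power and the planned analysis are untouched. If f = 0.25 was meant, 98 is right; if a partial eta squared of 0.25 was really meant, 98 is more than enough. No test, estimate or decision rule uses the planning value. The word medium points towards f, and the plan sets no target against which an observed partial eta squared is to be judged, so a misreading of the results is a risk and not a certainty. All of this stands, and it limits the weight of the point. It does not make the sentence true: the printed inputs do not yield the printed N, and nothing elsewhere in the article corrects them.

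A second objection is that the sample size section names neither three measurements nor the interaction test, and that another design also gives 98. That is correct. The exact settings are an inference that the authors need to confirm. The conclusion about the label does not rest on them.

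A reader might go further and infer that the trial is underpowered, or that it is at fault for not being sized on the comparison of intrinsic-foot-muscle training with control. The article supports neither. Power is adequate on both readings of 0.25. The planned analysis is an omnibus comparison of three groups over time with Bonferroni post hoc tests, and sizing the trial on such an omnibus test is consistent with that plan.

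**Conclusion.** The label is wrong as written. At alpha 0.05, power 0.80 and three groups, N = 98 is obtained with 0.25 as f(V), equivalent to a partial eta squared of 0.059. A partial eta squared of 0.25 would need about 21 participants. The planned effect is overstated 4.25-fold in variance explained, or 2.3-fold in f.

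The exact match assumes the group-by-time interaction with three measurements, as in the analysis section. That no tested variant with partial eta squared 0.25 comes near 98 holds without that assumption. The required number and the recruitment target both stand, so this is a correction to a stated figure and its severity is modest. It is still worth making, because the figure is the sole basis given for the trial size and is expressed in the metric in which results will be reported.

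**What to change.** Restate the sentence in Sample size {14} along these lines: effect size f(V) = 0.25 (partial eta squared about 0.06), repeated-measures MANOVA, within-between interaction, 3 groups, 3 measurements, alpha 0.05, power 0.80, required total 98; recruiting 120 allows for about 18% drop-out. Before publishing it, the authors should check the test, the number of measurements and the effect size entry against their saved G*Power output, since these settings are inferred here.

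The cost is one sentence. N, recruitment and the analysis do not change.

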#### Recruitment {15}

The participants will be recruited through advertisements from several community centres in Shanghai, China. All participants will be screened by the research team (clinicians, physical therapist and exercise specialists) for participation based on the inclusion and exclusion criteria listed above. Those who satisfy the inclusion criteria and are willing to participate in this experiment will be provided details about study treatment, follow-up and contact details for further information. Each participant will be informed of the benefits and possible risks, and they will sign the informed consent and an ethics committee-approved personal information sheet before their inclusion in the study. Recruitment will begin in October 2020.

### Data collection and management

#### Plans for assessment and collection of outcomes {18a}

Before the trial, all researchers responsible for data collection will be trained to be proficient in test procedures and operations. The questionnaires and laboratory tests used in this study have been widely used in previous studies, and reliability and validity have been reported in the study. Outcome measurements and data collections will be conducted at the baseline, post-intervention (12 weeks) and follow-up (24 weeks).

#### Plans to promote participant retention and complete follow-up {18b}

During the 12-week follow-up, participants will be asked to maintain their previous lifestyle and continue their interventions respectively. The physical therapist will provide guidance by telephone weekly. At week 24, the participants will return to the laboratory and be assessed again.

#### Data management {19}

EpiData 3.1 software will be used for data entry. To promote the quality and accuracy of data, double data entry and checking will be managed by two independent administrators. The data obtained in this study will be stored in an electronic database. The data administrators and statistician will be the only ones with access to the information. They will also be responsible for data backup. Original case report forms and any other records will be archived at Shanghai University of Sport for a minimum of 5 years from the study end.

#### Confidentiality {27}

The information collected will be used for research purposes and be analysed without the identification of the individuals involved. All the personal information of potential and enrolled participants will not be shared or released. At the end of the trial, all information will be archived at Shanghai University of Sport.

#### Plans for collection, laboratory evaluation and storage of biological specimens for genetic or molecular analysis in this trial/future use {33}

Not applicable because no samples will be collected.

### Statistical methods

#### Statistical methods for primary and secondary outcomes {20a}

The full analysis set includes all randomised participants who take at least one session of intervention. If follow-up data of primary outcomes are missing, last observation carried forward method and multiple imputation method will be carried out to adjust for the missing data and intention-to-treat analysis was utilised.

The statistical analyses, including calculation of the mean and standard deviation, will be performed using SPSS statistical software (version 20.0 for Windows; SPSS, Inc., Chicago, USA). Descriptive statistics will be used separately for every group and for the total sample. Continuous variables will be presented as means, standard deviation, and 95% confidence intervals. And categorical variables will be expressed percentages and absolute numbers. The normality of distribution for quantitative data will be assessed using the Kolmogorov–Smirnov test. Chi-squared tests or Fisher’s exact tests (categorical variables) and one-way ANOVA or nonparametric tests (continuous variables) will be used respectively to test the demographic differences among the IFM, EFM and control groups.

The average effects (difference between the three groups) for all the variables will be estimated using general linear models of multivariate of analysis for repeated measurements (MANOVA) test, which incorporates the three intervention groups (control * IFM * EFM), time (baseline * post-intervention * follow-up) and group-time interaction. To examine the effect size of the treatment, the partial eta squared will be calculated. Bonferroni’s post hoc test will be applied to identify the differences. Once the significant difference of group-time interaction is detected, the one-way repeated measurements will be performed to determine the difference of effect within each group (pre-intervention, post-intervention and follow-up). Statistical significance will be set at 0.05 for all analyses. Analysis will be carried out by an independent researcher.

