#### Primary outcome measures

##### Static postural stability

The NeuroCom Balance Manager System (Version 9.3, Copyright ©1989–2016 Natus Medical Incorporated) will be used to determine static postural stability. The balance platform is equipped with 18×60″ dual-force plate to measure the changes in COP of each participant. The COP will be collected when the participants stand on both feet with eyes open or eyes closed. We will calculate the same parameters as the postural stability test during standing: total length (TL), sway area (SA), maximum range of sway in the diction of AP, maximum range of sway in the diction of ML, mean velocity of COP sway and coefficient of variance of COP sway. The outcome data of static postural stability will be formatted as the difference at the points of baseline (week 0), post-intervention (week 12) and follow-up (week 24). The values will be shown as mean and standard deviation.

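### The planned interaction test is valid but omnibus; the between-group estimate averages in baseline, and a significant interaction is resolved within arms, so no post-treatment IFM-versus-control contrast is fixed

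*Protocol article*

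**What the plan says.** The section on statistical methods for primary and secondary outcomes {20a} of the protocol article describes one model for every outcome: "The average effects (difference between the three groups) for all the variables will be estimated using general linear models", in the form of a repeated-measures MANOVA. Its terms are the three groups, time with baseline as one of three levels, and the group-time interaction. A Bonferroni post hoc test is to identify differences; neither the factor nor the visit is given. After a significant interaction, the named next step is that "one-way repeated measurements will be performed to determine the difference of effect within each group". On error level, "Statistical significance will be set at 0.05 for all analyses".

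The sample size section {14} uses "power (1 − β) = 0.80" and a "standardised medium effect size = 0.25 (the partial eta squared"), concludes that "three independent groups with 98 participants in total were the required sample size", and allows for drop-out: "40 participants in each group will be recruited for this study".

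The static postural stability section, which defines the primary outcome, adds: "The outcome data of static postural stability will be formatted as the difference at the points of baseline (week 0"), and likewise at weeks 12 and 24.

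**The concern.** The trial asks whether intrinsic-foot-muscle exercise adds something to lower extremity resistance training. That needs a comparison of IFM with control, and of IFM with EFM, after treatment. Two features of the stated analysis work against this.

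First, the group effect is averaged over visits that include one taken before treatment. Randomisation makes the expected baseline difference zero, so including that visit pulls the average towards zero.

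Second, the plan leaves the randomised comparison just when it has found something. A significant interaction says that change differs somewhere among the three arms. The plan then looks at change inside each arm. The interventions section gives all three arms the same supervised resistance training, so all may improve whatever the foot exercise contributes. Significance in IFM and not in control is no test of the difference between them, and significance in both says nothing about which is better.

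At stake is the main conclusion: it could rest on before-after tests, or on a between-group estimate that understates the post-treatment effect.

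**Working it through.** **1. The plan's own figure.** Inputs from the sample size section: 3 groups, alpha 0.05, power 0.80, effect size 0.25; 3 visits come from the outcomes section. For the group-time interaction in a repeated-measures MANOVA (Pillai), k = 3, p = 3 − 1 = 2, q = 3 − 1 = 2 and s = min(p, q) = 2.
- df1 = p × q = 4
- df2 = s(N − k − p + s) = 2(98 − 3 − 2 + 2) = 190
- noncentrality = s × N × f² = 2 × 98 × 0.25² = 12.25
- power = 0.8005

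So 98 is reproduced when 0.25 is read as Cohen's f; read literally as partial eta squared, the same calculation gives 21. The sizing therefore matches the interaction. For the averaged group effect with f = 0.25, the total would be 86, 106 or 127 at correlation 0.3, 0.5 or 0.7.

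**2. What the averaged group effect estimates.** Let d be the true IFM-control difference, with zero expected difference at baseline.
- Effect equal at weeks 12 and 24: (0 + d + d)/3 = 0.67d
- Effect at week 12 only: (0 + d + 0)/3 = 0.33d

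The interaction is not affected, because baseline serves there as the reference for change.

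**3. Effect on pairwise power.** The protocol gives no SD or within-person correlation (rho), so these are assumptions: SD 1, compound symmetry, d = 0.6 SD at both post-baseline visits, 33 per arm (98/3 rounded up), unadjusted two-sided 0.05, noncentral t with 64 degrees of freedom.
- Averaged contrast: effect 2d/3 = 0.40, variance per person (1 + 2·rho)/3
- Baseline-adjusted week 12: effect d = 0.60, variance per person 1 − rho²
- Standard error in each case: √(2 × variance/33)

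| rho | Averaged: variance, SE, effect/SE | Power | Week 12 adjusted: variance, SE, effect/SE | Power |
|---|---|---|---|---|
| 0.3 | 0.533, 0.180, 2.22 | 59% | 0.910, 0.235, 2.56 | 71% |
| 0.5 | 0.667, 0.201, 1.99 | 50% | 0.750, 0.213, 2.81 | 79% |
| 0.7 | 0.800, 0.220, 1.82 | 43% | 0.510, 0.176, 3.41 | 92% |

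The ordering holds under a Bonferroni level of 0.05/3 with 40 per arm and d = 0.5: 35%, 28% and 23% for the averaged contrast, against 47%, 56% and 76% for adjusted week 12.

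The ratio of (effect/SE)² for adjusted week 12 over the averaged contrast is [1/(1 − rho²)] ÷ [(4/9)/((1 + 2·rho)/3)]: 1.3 at rho 0.3 and 2.0 at rho 0.5.

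**4. The interaction under the same assumptions.** With d = 0.6 in IFM only and 33 per arm, simulation gives the interaction about 72% power at rho 0.5 and about 92% at rho 0.7. It is thus not a weak test. What it lacks is an estimate of IFM minus control: EFM differing from control could also make it significant.

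**The case against.** The strongest reply is that the plan already contains a sound between-group test. The interaction compares change between randomised arms, is undiluted, reproduces the stated 98, and comes close to the power of the adjusted week-12 contrast (about 72% against 79% at rho 0.5). All of this stands. A reader might infer that the whole efficacy analysis is diluted by a third; the documents do not support that, because the dilution touches only the averaged group effect and any post hoc test on the group factor.

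A reader might also infer that IFM is never compared directly with control. That is not established. The Bonferroni test names no factor or visit, so pairwise comparisons at each visit are compatible with the text. Equally, nothing excludes pairwise comparisons of the averaged group means, which would carry the dilution.

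A third tempting inference is that equal improvement in all arms would often yield conflicting within-arm results that are then read as treatment effects. The plan runs within-arm tests only after a significant interaction. With 33 per arm, rho 0.5 and equal improvement of 0.45 to 0.55 SD, simulated discordance behind that gate is about 3–4%. The remaining problem arises when the gate opens: the within-arm tests cannot say which arms differ.

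One may add that an article leaves exact contrasts to a full protocol or SAP. That would excuse silence, but here the article names the follow-up procedure, and it is the wrong kind.

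The wording about a difference at baseline could be read as change scores, which would be zero at week 0. The dynamic postural stability section speaks of scores at the same visits, so this is an editorial ambiguity and no more.

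**Conclusion.** The point holds in a limited form. The omnibus interaction test is valid and should not be criticised as diluted. The defects are that the stated between-group estimate averages in a pre-treatment visit, that the post hoc comparison is not tied to a factor or visit, and that a significant interaction is resolved by within-arm tests that cannot answer the trial's question.

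The estimate shrinks by one third if the effect is equal at weeks 12 and 24, and by two thirds if it is present at week 12 only; both figures assume zero expected baseline difference. The loss of pairwise power against a baseline-adjusted week-12 contrast is 12, 29 and 49 percentage points at correlation 0.3, 0.5 and 0.7. Those figures rest on an assumed effect, SD and correlation structure that the protocol does not supply; the direction is the same across the range examined.

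**What to change.** Keep the group-time interaction as the omnibus test if wanted. For the primary estimates, fit a linear model to the week 12 and week 24 values with arm, visit, arm-by-visit, baseline value and baseline-by-visit. Name IFM minus control and IFM minus EFM at week 12 as the primary contrasts, Bonferroni-adjusted, with 95% confidence intervals. Report the week 24 contrasts separately. State that within-arm changes are descriptive and not evidence of efficacy. In the outcome sections on static stability and walking, say that measured values at each visit are analysed.

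The cost is a change of wording. Baseline, week 12 and week 24 values are already collected, and no extra participants, visits or measurements are needed.

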##### Dynamic postural stability

To develop the study, the NeuroCom Balance Manager System (Version 9.3, Copyright ©1989–2016 Natus Medical Incorporated) will be recruited to determine postural stability by measuring the participants’ centre of gravity (COG) alignment at a sampling frequency of 100 Hz. The balance platform is equipped with 18×60″ dual-force plate to measure the vertical forces exerted through the participant’s feet. We will conduct the sensory organisation test (SOT) and limits of stability test (LOS) to evaluate the static postural stability. Similarly, the participants will be informed of all procedures in advance. They will be positioned with standardised foot placement relative to individual height and be instructed to stand facing forward, with their arms relaxed at their sides and to remain as still as possible. The participants will remove all footwear and be restricted by a seat belt.

For the SOT, the participants will perform all balance trials and repeat each trial three times [32]. The movements of COP will be recorded with the participants standing under six conditions (as shown in Table 1). The duration of running each condition was 20 s. In all trials, the assessor will not alert the participants to impending changes of surrounding or the platform, but the assessor will only instruct them to open or close their eyes. Each participant will complete these six trials in the random order.

**Table 1 Tab1:** Six conditions in sensory organisation testing

Test condition	Eyes	Surroundings	Platform
1	Open	Fixed	Fixed
2	Closed	Fixed	Fixed
3	Open	Sway referenced	Fixed
4	Open	Fixed	Sway referenced
5	Closed	Fixed	Sway referenced
6	Open	Sway referenced	Sway referenced

By the combination of vision, surrounding and contact surface, the SOT test creates sensory-conflict situations and helps to evaluate the capacity to maintain postural stability under these sensory conflicts. According to the sway and sway velocity of COP, the system will generate equilibrium scores of each condition. An overall composite equilibrium score will be calculated using a weighted average of these scores and be used for analysis. A high equilibrium score means a low postural sway, indicating greater postural stability [33].

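### The primary outcome is a set of COP variables with no lead variable, each tested at 0.05, so the primary conclusion has no controlled error rate; the sample size covers one test on one variable

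*Protocol article*

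**What the plan says.** The section Static postural stability is the only entry under primary outcome measures. It lists "total length (TL), sway area (SA), maximum range of sway in the diction of AP, maximum range of sway in the diction of ML", followed by "mean velocity of COP sway and coefficient of variance of COP sway". On test conditions it says "The COP will be collected when the participants stand on both feet with eyes open or eyes closed". Values are to be reported at baseline, week 12 and week 24. Neither a composite nor a lead parameter, eye condition or time point is given.

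The section Statistical methods for primary and secondary outcomes {20a} says that the average effects "for all the variables will be estimated using general linear models of multivariate of analysis for repeated measurements (MANOVA) test", with terms for group, time and their interaction. It names a Bonferroni post hoc test for locating differences and then sets one rule: "Statistical significance will be set at 0.05 for all analyses".

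The Sample size section {14} describes one repeated-measures MANOVA with three groups, alpha 0.05, power 0.80 and an effect size of 0.25. It arrives at 98 participants, raised to 40 per group (120) for drop-out. It does not mention several primary variables.

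**The concern.** Six parameters in two eye conditions make 12 primary variables. Each gets its own test at 0.05, and nothing says how many must be positive, or which one, before the intervention is called effective. A significant result on any of them could be reported as a positive primary outcome. The Objectives section says that the results will determine effectiveness, so the primary analysis is meant to be confirmatory. A confirmatory claim needs an error rate that is fixed in advance for the claim as a whole, and the stated rule fixes it only for each variable.

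The sample size raises the same question. If the power calculation is for one test, the 80% belongs to a variable that the protocol never identifies.

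**Working it through.** **1. Reproducing the 98.** Inputs from Sample size {14}: 3 groups, alpha 0.05, power 0.80, effect size 0.25. From the outcome section: 3 time points. For the group-by-time interaction on one variable (Pillai trace) there are p = 2 time contrasts and s = 2:

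- df1 = 2 × 2 = 4
- df2 = 2(N − 3) = 190 at N = 98
- non-centrality = N × s × f² = 98 × 2 × 0.0625 = 12.25
- power = 0.8005 at N = 98, and 0.796 at N = 97

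So 98 is reproduced exactly as one interaction test on one variable. This takes 0.25 as f(V). Read as a partial eta squared, which is how the text labels it, 0.25 would give N = 21. That labelling is a separate matter. A joint test over 6 or 12 dependent variables at the same f would need 145 or 190.

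**2. Number of primary variables.** 6 parameters × 2 eye conditions = 12. If recording time is fixed, mean velocity equals total length divided by that time, so one parameter per condition is redundant and 5 × 2 = 10 distinct variables remain. If the eye conditions are not analysed separately, there are 6.

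**3. Chance of at least one false positive, one 0.05 test per variable.** With independent tests this is 1 − 0.95^K:

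- K = 12: 1 − 0.5404 = 46.0%
- K = 10: 1 − 0.5987 = 40.1%
- K = 6: 1 − 0.7351 = 26.5%

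The protocol gives no correlation among the COP variables, so equal correlation is assumed. The other rows come from simulating the interaction test with 99 participants and no true effect. Separate runs differ by about one percentage point.

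| Assumed correlation | 12 variables | 10 variables | 6 variables |
|---|---|---|---|
| 0 (formula) | 46% | 40% | 26% |
| 0.5 | 33% | 30% | 21% |
| 0.7 | 25% | 23% | 17% |
| 0.9 | 14–15% | 13% | 11% |
| 0.95 | 11–12% | 10–11% | 9% |

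These figures count one test per variable. Treating the group effect and the interaction as separate routes to success would raise them.

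**4. Power if alpha were split.** Bonferroni over 12 gives 0.05/12 = 0.00417. With the same f(V) = 0.25, power per variable is 47% at N = 98 and 62% at N = 120. Restoring 80% needs N = 158.

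**5. Power if one variable leads.** Alpha stays at 0.05 and the 98 stands as calculated for the group-by-time test on that variable. A test at a single time point has 2 degrees of freedom instead of 4, and its power depends on how much of the assumed effect falls there. If that contrast has f = 0.25, power is 58% at N = 98. If it carries the whole assumed effect (V = 2 × 0.0625/1.0625 = 0.118, so f = √(0.118/0.882) = 0.365), power is 90%.

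**The case against.** - **A MANOVA over all the variables could be one joint test, which holds the overall error at 5%.** The described terms are group, time and group-time interaction, which is a MANOVA over time points. The 98 does not fit a joint test on 6 or 12 variables, and no gatekeeping from a joint test to single variables is described. This reading does not stand.
- **Bonferroni might extend across variables.** The text does not exclude it in so many words. As a post hoc test for locating differences it ordinarily covers comparisons within one variable, and the blanket 0.05 rule points the same way. It is fair to say only that no adjustment across variables is stated.
- **COP parameters come from the same sway trace and are correlated.** This stands, and it limits the size. A reader might infer that the trial has a 46% false-positive rate. The documents do not support that: 46% needs 12 independent tests, which is impossible if mean velocity duplicates total length. Nor is 15% a floor, since higher correlation gives less.
- **The duplication is itself assumed.** No recording time is given for the static test; the 20 s belongs to the sensory organisation test.
- **Testing other variables does not reduce power on any one of them.** This is correct. The 80% is not wrong per variable, and the 47% arises only if alpha is split over 12.
- **The secondary balance tests might count as primary**, because the protocol says "We will conduct the sensory organisation test (SOT) and limits of stability test (LOS) to evaluate the static postural stability". This should not be inferred. The sentence stands under the secondary heading Dynamic postural stability, and the end of that section calls both tests dynamic. The word is a slip and adds no primary variable.
- **A separate analysis plan could settle it.** An adjustment there would contradict the alpha rule stated here and would lower the power claimed here.

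**Conclusion.** The point holds. The protocol fixes several primary variables without a lead and a 0.05 rule without a stated adjustment across them, so the error rate of the primary conclusion is not controlled. The stated power applies to each variable singly.

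The size rests on two assumptions: how many variables are analysed, and equal correlation among them of 0 to 0.95. The inflated error runs from about 9% (six variables, correlation 0.95) to 46% (12 independent variables). No scenario examined brings it down to 5%, but the documents do not allow one figure to be singled out. This needs correcting before outcome data are seen by group, because a lead variable chosen afterwards would not be credible.

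**What to change.** **Preferred.** By a documented amendment, before any unblinded look at outcome data, the investigators name one COP parameter, one eye condition and one time point as the primary outcome, tested at 0.05. Which ones is for them to choose; the protocol gives no basis for a choice from outside. The remaining COP variables and time points become secondary, either Holm-adjusted or labelled supportive. No alpha is split, so the 98 remains valid for the group-by-time test on the named variable. If the decisive test is a contrast at the named time point alone, its power should be stated too.

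**Alternative.** Keep several primary variables, adjust across them by Holm or Bonferroni, and restate the power: with Bonferroni over 12, about 47% per variable at 98 participants and 62% at 120.

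**Cost.** No extra participants under the preferred option, but fewer variables can carry a confirmatory claim. The Trial status section has recruitment starting on 1 February 2021, so this is an amendment to a running trial. The section on communicating protocol amendments {25} requires it to be reported to all investigators, participants, the registry and the ethics committee.
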